## Methods/Study design

To undertake the overall objective of the proposed research, the empirical research is divided into 3 studies:Qualitative longitudinal researchQualitative longitudinal research (QLR) is a relatively recent development which has yet to be fully articulated as a coherent methodology [72]. It embodies a range of in-depth interviews which involve returning to interviewees to measure and explore changes which occur over time and the processes associated with these changes [73]. This novel approach is very relevant for this research proposal as sustainable healthy eating behaviour is not explored yet in Poland.Twenty interviews will be carried out in three time periods in order to get insights on consumers’ attitudes, knowledge and perception as well as current behaviour towards sustainable healthy eating. The selection of issues in the topic guide will be based on the outcome of the literature review. However, based on current understanding, the six principles introduced in the campaign “Livewell 2020” will be used as a starting point to discuss different elements of sustainable healthy eating with the interviewees. Participants will be recruited from the local area by advertisements made in local newspapers and on local websites. The target group of our intervention will be young adults (aged 18-30). Young adults often establish unfavourable dietary habits when leaving the parental home, i.e. consuming a diet of limited variety, high snacking, consuming more high-fat foods (including fast foods), more soft drinks, and less fruit and vegetables e.g. [74]. Such habits may have a long-lasting impact on their own health or the health of their future families [75, 76]. Young adults are also the future or current young parents. Therefore, it is important to explore the sustainable healthy eating behaviour to this particular group. The sample will consist of two groups: one more interested in sustainability issues and second consisting of people not specifically focused on sustainability issues. The three waves of interviews will be transcribed verbatim for subsequent analyses. Transcripts will be analysed systematically to capture three critical elements: time, process and change. Reporting of the findings from this qualitative study will adhere to COREQ guidelines [77].Quantitative survey (SHE index)Although obesity and climate change are two of the hottest topics in the food-related research, up to date, there is no agreed definition of sustainable healthy diet. Validated measurement scales for healthy eating (e.g. interest in healthy eating [33], healthy eating index [34] and for sustainable behaviour (e.g. index of sustainability of food practices [37] exist. This study aims to develop an index that measures a consumer’s sustainable healthy eating behaviour.Based on the literature review and information collected through in-depth interviews a questionnaire will be developed, pre-tested and validated on a judgment sample of 200 young respondents in Warsaw and Mazovian region [78]. Judgment sample is a type of non-random sample, which is selected based on the opinion of the experts [79]. The preliminary questionnaire will be designed to assess a wide range of sustainable healthy eating behaviours such as: purchase of local foods, meat, dairy and plant consumption, portion size, processed food consumption, food packaging, seasonal food. SHE Index will be validated by means of convergent and discriminant validity as indicated by Hair and co-authors [80]. The developed measure will be used as an outcome measure in Study 3 as described below.Randomised controlled trialConsumer research mostly uses a cross-sectional design to measure perceptions, attitudes, and their association with behaviour [38]. However, using an experimental design, such as a randomised controlled trial (RCT) has many advantages since it eliminates some biases, for instance “selection bias” (pre-existing differences), “omitted variable bias” and partly “publication bias” (supporting results that are statistically significant) [39]. A systematic review study in developed countries suggests that the omitted variable bias is a major problem when non-experimental methods are used [40].This research design assigns subjects randomly to either a study or a control group (Fig. 2). The study group experiences an intervention or experiment while the control group does not. Both groups are observed at two points in time, before (baseline) and after (follow-up) an intervention or experiment. The integrative model will be adapted after Study 1 (in-depth interviews to the specific case of sustainable healthy eating behaviour in Poland). As in Study 1 the target group of our intervention will be young adults (aged 18-30).

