
**Fig. 2 Fig2:**
[figure not shown]
Study 3 flow diagram

The content of the intervention build on the results of Studies 1 and 2 and will be assessed in a small pre-pilot. Around 10 participants from a convenience sample will be recruited for the pre-pilot. Feedback on the interventions will be collected by a short questionnaire with open-ended questions. Then, about 200 Polish consumers will be recruited for the pilot RCT. A stratified design will be used to recruit 18-30 years old adults using Internet and mobile phones for the intervention. The sample will be represented for gender and region. Recruitment of the sample as well as baseline and follow-up surveys will be done by a professional market agency in accordance with ICC/ESOMAR – International Code of Conduct for Market and Social Research. Highly qualified and experienced interviewers will carry out face-to-face interviews at home using a CAPI approach (Computer Assisted Personal Interviewing). Use of a professional market agency for recruitment and data collection is beneficial for the project in a way that the sample will be geographically wide, will include spread of socio-economic characteristics and data will be collected relatively fast. The sample will be randomly allocated into a treatment group and a comparison control group that never received the treatment as recommended by Schulz and Grimes [39]. Eligible participants will be randomised in a 1:1 ratio to either the intervention or control group, stratified by gender. A computer generated randomisation sequence with variable block sizes of 2 or 4 will be used. The group allocation will be concealed until the point of participant randomisation. Researchers will be blind to group allocation.

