After the randomisation the participants will complete a baseline survey that includes the measure developed in Study 2 and extended by questions measuring different psychometric variables, such as consumer attitudes, norms, subjective and objective knowledge, involvement or self-efficacy (Fig. 1). The SHE index developed in Study 2 will be used as a dependent variable. A relative change in the SHE index will be used as a primary outcome. The intervention will be considered as successful (effective) when a meaningful change in the primary outcome will take place, i.e. the SHE index will increase by 5 %. We are aiming for a total sample size of 220 which will allow us to detect an effect size (measured by Cohen’s d statistic) of 0.44 for the SHE index. This would be considered a ‘medium’ effect size. The data collected in the pilot trial will allow us to refine our sample size estimates for the main trial.

A segmentation analysis will be carried out on consumers’ knowledge, attitudes and dietary habits from the baseline survey in order to obtain different groups of consumers who will receive tailored messages.

Tailoring messages has been proven to be an effective health education approach [81, 82]. Research in computer-mediated health education has indicated that adapting and tailoring health content to the individual can increase their engagement, improve leaning, foster positive attitudes about behaviour change and enhance health intentions e.g. [82–84]. Additionally, there is evidence that computer-tailored nutrition education is a more effective tool for motivating people to change to healthier diets than general nutrition education [70].

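### The primary outcome and its 5% success rule are a relative change in a questionnaire index with no stated zero, so both depend on item coding; a per-person percent change would also cost power

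*Protocol article*

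**What the plan says.** All references are to the protocol article, Methods/Study design.

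- Source of the index (Study 2): "The preliminary questionnaire will be designed to assess a wide range of sustainable healthy eating behaviours". The response scale, the scoring and the zero are not given, because Study 2 has yet to produce them.
- Primary outcome (Study 3, text after Fig. 2): "The SHE index developed in Study 2 will be used as a dependent variable", followed by "A relative change in the SHE index will be used as a primary outcome".
- Success rule, same paragraph: a meaningful change, "i.e. the SHE index will increase by 5" per cent. No control-arm reference is attached to this figure.
- Sample size, same paragraph: "We are aiming for a total sample size of 220", said to be enough to "detect an effect size (measured by Cohen’s d statistic) of 0.44 for the SHE index". The preceding text says that "about 200 Polish consumers will be recruited for the pilot RCT".
- Randomisation: participants are "randomised in a 1:1 ratio to either the intervention or control group, stratified by gender".
- Analysis (last paragraph of Methods): two-sided tests at 5%, intention-to-treat, and structural equation modelling (SEM) to evaluate effectiveness. No covariate list is given for the primary outcome.

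**The concern.** A percent change is meaningful when zero means none of the quantity. For a summed or averaged questionnaire score, zero is a coding choice. With relative change as the primary outcome, the same answers from the same people can meet or miss the 5% rule according to how Study 2 scores the items.

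There is a second problem if the ratio is taken person by person. Each person's change is divided by a baseline measured with error. This skews the outcome, gives people with low baselines the most influence and adds variance. The baseline value would be more useful as a covariate.

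At stake are whether the headline result and the success verdict can be interpreted, and possibly some of the power that 220 participants would provide.

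**Working it through.** **1. The plan's own sample size.** Inputs from the article: d = 0.44, two-sided alpha 0.05, 1:1 allocation. Power is not stated. With n per arm = 2(z_0.975 + z_power)²/d²:

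- 90% power: 2(1.960 + 1.282)²/0.44² = 108.5, so 109 per arm and 218 in total.
- 80% power: 2(1.960 + 0.842)²/0.44² = 81.1, so 82 per arm and 164 in total; 164/0.75 = 219 with an assumed 25% dropout.

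Either route reproduces 220. Cohen's d does not change when a constant is added to the index. The sample size is therefore free of the coding problem, but the primary outcome is not.

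**2. Dependence on coding.** If every item score is lowered by a constant c, relative change goes from (Y − X)/X to (Y − X)/(X − c). The numerator is unchanged and the denominator is not. The scales below are illustrations, since the article gives none.

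| Same answers, same gain | First scoring | Second scoring |
|---|---|---|
| Gain 0.20 | 1-7, mean 4: 0.20/4 = 5.0% | 0-6, mean 3: 0.20/3 = 6.7% |
| Gain 0.15 | 1-5, mean 3: 0.15/3 = 5.0% | 0-4, mean 2: 0.15/2 = 7.5% |

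Read the other way, in the first row the 5% rule asks for 0.20 points under one coding (0.05 × 4) and 0.15 points under the other (0.05 × 3). A difference in follow-up SHE adjusted for baseline is the same, in index points and in p-value, under either coding. This step needs no assumption about correlation or spread.

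**3. Power, if relative change is computed per person.** The article gives neither the baseline/follow-up correlation (rho) nor the CV of the index, so both are assumed. One CV can be inferred from its figures: if 5% and d = 0.44 describe the same effect, CV = 0.05/0.44 = 0.114.

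For follow-up adjusted for baseline, the residual SD is √(1 − rho²) index SDs, so power ≈ Φ(0.44/√(1 − rho²) × √(110/2) − 1.96). At rho = 0.5 this is Φ(0.508 × 7.416 − 1.96) = Φ(1.81) = 96.5%. For percent change, trials were simulated with normal baseline and follow-up, an additive effect of 0.44 SD, 110 per arm and a t-test on (Y − X)/X.

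| rho | CV | Percent change, unadjusted | Follow-up adjusted for baseline |
|---|---|---|---|
| 0.4 | 0.20 | about 75% | 94% |
| 0.5 | 0.114 | about 88% | 96% |
| 0.5 | 0.20 | about 85% | 97% |
| 0.7 | 0.20 | about 97% | 99.6% |
| 0.8 | 0.114 | no loss | no loss |

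Repeat simulations agree within one or two percentage points.

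**4. If percent change is itself adjusted for baseline.** At rho 0.5, power rises to about 96% at CV 0.114 and 94% at CV 0.20. Most of the loss is recovered at these CVs. The dependence on coding from step 2 remains.

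**The case against.** Four objections carry weight.

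- The article names no test or covariate list for the primary outcome. The planned SEM can carry baseline SHE and gender, and an article commonly leaves such detail to the full plan. The unadjusted t-test in the table is an assumed comparator, so the power loss cannot be charged to the plan as a fact.
- Relative change may mean the change in the group mean divided by the baseline mean; the wording of the 5% rule fits that too. The noisy individual divisor and the skew then disappear. The coding problem does not.
- Rho and CV are not in the documents. At rho 0.7 or above with a modest CV, the loss is a few percentage points or nothing.
- The remedy replaces the stated primary outcome and touches fieldwork, so it is more than a change of wording.

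Three stronger readings are tempting but unsupported. A reader might infer that the standard error ignores the gender stratification; the article states no standard error or model terms from which that could follow. A reader might infer that, because a mean of individual ratios drifts upward even when nothing changes, the trial is biased towards a positive result. Under no effect the same drift is expected in both randomised arms and cancels in their difference; it would matter only if the 5% rule were read within one arm, which is a separate question. A reader might also infer much larger power losses at a CV near 0.30, but those results turn on how near-zero baselines are handled and are not reproducible enough to use.

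**Conclusion.** The point holds in a limited form. The article itself fixes a relative change and a 5% threshold on an index whose scoring and zero are not stated, so this is not detail left to a later document. The dependence on coding is plain arithmetic and applies to individual ratios and group means alike: in the illustration, the same gain is 5% or 6.7%. It rests on one inference, that a questionnaire index with no stated zero has an arbitrary one.

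The power loss is secondary and conditional. It arises only if the ratio is formed per person, and it is largest if the comparison is unadjusted. Over the assumed values shown, it runs from none (rho 0.8, CV 0.114) to about 19 percentage points (75% against 94% at rho 0.4, CV 0.20). In none of the settings examined did percent change have more power than follow-up adjusted for baseline. This is a change that should be made; it does not invalidate the trial.

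**What to change.** - Define the primary outcome as the SHE index at follow-up.
- Compare arms by linear regression, or the equivalent SEM path, with baseline SHE and gender (the stratification factor) as covariates. Report the adjusted mean difference with its 95% CI.
- Once Study 2 has fixed the scoring, restate the 5% criterion as a between-arm difference in index points.
- Keep percent change as a descriptive figure only.
- Complete the baseline survey before allocation is revealed. The article places it after randomisation, and a covariate should not be open to influence from knowledge of the arm.

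The cost is small but not nil. The primary outcome and success rule must be reworded, and the order of survey and allocation changed in the field. No new data are needed: baseline SHE, follow-up SHE and gender are already collected, and the named software fits the model. The new outcome also matches the sample size statement, which is given for the SHE index and not for its relative change.

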The intervention will take 1 month. The six behaviours introduced in the campaign “Livewell 2020”: eat more plants, waste less food, eat less meat, eat less processed food, eat variety of food, and eat more certified food will be explored during the interviews, adapted to the Polish context and communicated to consumers. The topics will be also refined based on findings from Studies 1 and 2. At the end of the intervention data for all of the users will be provided with the content of the messages that were sent and information whether the participants clicked through to read the page and how much time they spent on the page. After the intervention participants will complete a follow-up survey consisting of similar variables as the baseline survey. The interaction with participants through the mobile application is expected to bring people to a desirable more rational and conscious behaviour as suggested on Fig. 1. All participants will be volunteering adults and will provide informed consent. The study will be submitted for clearance to the local ethical committee.

Subsequently all data, also the data from the questionnaires, will be analysed using statistical software programs: SPSS 22.0 and LISREL 9.1. All statistical tests will be two-sided at the 5 % significance level. All treatment evaluations will be performed on the principle of intention-to-treat (ITT), using the observed data collected from all randomised participants. Appropriate imputation methods will be applied to the missing data on the primary outcome. A cluster analysis will be used to identify consumer segments based on their knowledge, attitudes and dietary habits. Structural equation modelling (SEM) will be applied in order to evaluate the effectiveness of the intervention, and particularly to explore the impact of different mediators and moderators (following the theoretical framework) on consumers’ behavioural intention and behaviour towards sustainable and healthy eating. SEM has not been extensively used in the experimental studies. The application of SEM in experimental studies represents a significant but relatively untapped potential area of application [87].

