## Discussion

The project approach is novel and original both in terms of the nature of the research questions being addressed and the methodologies envisaged to be employed. To date sustainability and healthy eating have not been readily combined in consumer behaviour research. The importance of and need for developing interventions aiming at increasing consumers’ sustainable healthy eating behaviour through influencing their attitudes, self-efficacy and knowledge about the topic has been highlighted [24]. Secondly, the use of longitudinal qualitative research with three separate time periods is a relatively recent methodological approach that has yet to be fully articulated as a coherent methodology [72]. It embodies a range of in-depth interviews which involve returning to interviewees to measure and explore changes which occur over time and the processes associated with these changes [73]. This novel approach is very relevant for this research proposal as sustainable healthy eating behaviour is not explored yet in Poland.

Thirdly, the use of randomized controlled trial (RCT) in social and agricultural economic science; and particularly in consumer research is innovative. Most of the studies use cross-sectional data, where the causal effects between the mediators and endogenic variables cannot be proven. In the experimental setting, such as a RCT we will be able to measure the actual links between the variables. Fourthly, the application of structural equation modelling as a technique to evaluate the effectiveness of the intervention as well as the role of different mediators and moderators is new. Only few studies have successfully applied this method so far e.g. [88]. Finally, the use of new technologies, such as mobile learning for providing information to consumers is innovative as well.

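### The plan gives an SEM with mediators the task of judging effectiveness without saying which SEM quantity counts, and wrongly credits randomisation with securing mediator-outcome links

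*Protocol article*

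**What the plan says.** In Methods/Study design, the analysis paragraph for Study 3 states that "Structural equation modelling (SEM) will be applied in order to evaluate the effectiveness of the intervention, and particularly to explore the impact of different mediators". The aim is said to cover moderators too, for both intention and behaviour. The Discussion repeats that the SEM serves both purposes, effectiveness and mediation. No other model for comparing the arms is named.

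Three other statements bear on effectiveness. The Study 3 outcome paragraph makes relative change in the SHE index the primary outcome and counts the intervention as effective if the index rises by 5 %. The same paragraph sizes the trial on the index itself: "We are aiming for a total sample size of 220", to detect a Cohen's d "statistic) of 0.44 for the SHE index". The analysis paragraph requires intention-to-treat for all treatment evaluations.

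On mechanism, the Discussion first says that cross-sectional data cannot prove causal effects between mediators and endogenous variables. It then continues: "In the experimental setting, such as a RCT we will be able to measure the actual links between the variables". On timing, Methods/Study design says: "Both groups are observed at two points in time, before (baseline) and after (follow-up) an intervention or experiment". The baseline survey holds the SHE index and the psychometric variables (attitudes, norms, knowledge, self-efficacy), and the follow-up survey repeats similar variables.

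**The concern.** Two things need separating.

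- **Which quantity decides.** A mediation SEM produces a direct path from arm to SHE, one or more indirect paths, and their sum. Only the sum is the effect of being assigned to the app. The direct path is what remains after conditioning on variables measured after randomisation. It shrinks as the theory in Fig. 1 proves more correct. An indirect path can be significant when SHE has not moved. A total from a model that drops the direct path is constrained by theory. The plan gives the SEM the task of evaluating effectiveness and excludes none of these readings.
- **What randomisation protects.** It protects the effect of arm on each mediator and of arm on SHE. It does not protect the mediator-to-SHE path. That path stays open to unmeasured common causes, to shared reporting error between scales answered in one survey, and to doubt about which changed first. The Discussion says otherwise.

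At stake are an app that works but is reported as ineffective, or a causal mechanism reported from an app that did not change SHE.

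**Working it through.** **Inputs from the protocol article.** Total N: "We are aiming for a total sample size of 220" (the recruitment text elsewhere says "about 200 Polish consumers will be recruited for the pilot RCT"). Effect: d = 0.44 on the SHE index. Level: "All statistical tests will be two-sided at the 5 % significance level". Allocation: "Eligible participants will be randomised in a 1:1 ratio to either the intervention or control group, stratified by gender", so 110 per arm. Neither power nor dropout is stated.

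**Assumed, not in the documents.** One mediator with within-arm SD 1, a linear model, complete data, and the mediator shifts and correlations given below.

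**1. The plan's own figure.** n per arm = 2(1.960 + 1.282)² / 0.44² = 2 × 10.51 / 0.1936 = 108.6, so 109 per arm and 218 in total. The stated 220 therefore fits 90% power with no dropout allowance. This is an inference: 80% power needs 164, and 164 / 0.75 = 219 fits as well. With 110 per arm, 0.44 × √55 = 3.263 and power = Φ(3.263 − 1.960) = 90%. With 200 in total, 0.44 × √50 = 3.111 and power is 87.5%. The sample size is not in error on this point.

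**2. Does splitting lose the randomised effect?** Let a be the effect of arm on the mediator, b the mediator-to-SHE path and c′ the direct path. In a linear SEM that keeps c′, total = c′ + ab. In simulation the two sides agreed in every scenario, with or without confounding. The randomised effect is therefore recoverable.

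**3. If the direct path were read as effectiveness.** Take a total of 0.44 with half mediated: a = 0.44, b = 0.5, ab = 0.22, c′ = 0.22, within-arm SD of SHE = 1.
- Residual variance of SHE given the mediator: 1 − 0.5² = 0.75.
- Variance inflation from the arm-mediator correlation: 1 + a²/4 = 1.048.
- SE(c′) = √(0.75 × 4/220 × 1.048) = 0.120.
- Power = Φ(0.22/0.120 − 1.960) ≈ 45%.

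A plain two-sample t-test at d = 0.22 gives 37%. Simulations with somewhat different scaling gave 38 to 47%. The range is therefore roughly 37 to 47%, against 90% for the total effect.

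**4. If an indirect path were read as a causal mechanism.** Suppose arm shifts the mediator by 0.44 SD, SHE does not change, the mediator has no effect on SHE, and a shared cause gives residual correlation ρ. The estimated b then tends to ρ, the indirect effect to 0.44ρ and the direct path to −0.44ρ, so the total is zero. Power for the arm-to-mediator path is 90%. Power for the mediator path is approximately Φ(atanh(ρ) × √216 − 1.960). The product is the chance that both are significant.

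| ρ | False indirect effect (SD) | Power, mediator path | Both significant |
|---|---|---|---|
| 0.2 | 0.09 | Φ(2.98 − 1.96) = 85% | 76% |
| 0.3 | 0.13 | Φ(4.55 − 1.96) = 99.5% | 90% |
| 0.5 | 0.22 | about 100% | 90% |

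Simulation agrees to within about three percentage points. The test of the total effect stays near 5% throughout. With ρ = 0 the false indirect effect is zero.

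**The case against.** The strongest reply is that effectiveness is not left to the SEM. The outcome paragraph defines success on the SHE index, the sample size rests on Cohen's d for that index, and intention-to-treat governs all evaluations. An SEM that keeps the direct path reports the total effect exactly. Its specification is also detail that a condensed article may leave to an analysis plan that is not shown here.

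Much of this stands. A reader might infer that the direct path will decide effectiveness, or that using an SEM forfeits the randomised comparison. The documents support neither: no sentence names the direct path as decisive, and the decomposition in step 2 shows that nothing need be lost. Nor is the missing SEM specification a fault in itself.

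Two things remain. The 5 % rule names no comparison with control and is not tied to the SEM, and intention-to-treat fixes who is analysed, not which path is read. So the role stated for the SEM, given twice, is not resolved by the other statements. And the Discussion sentence is a positive misstatement that no further analysis detail would cure.

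It is also fair to say that the mediator-SHE association is more than a single cross-section. Baseline values of both are collected and allow partial adjustment. They do not remove causes that change over time, shared reporting error at follow-up, or doubt about order.

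**Conclusion.** The point holds in two parts. First, the plan assigns effectiveness to a mediation SEM without saying that the total effect decides. The randomised effect would be misjudged only if a direct path, an indirect path, or a total constrained by omitting the direct path were read as effectiveness; the plan does not exclude this. Second, the Discussion is wrong to carry the protection of randomisation over to mediator-outcome links.

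The sizes in steps 3 and 4 illustrate the risk and do not forecast results: the mediator shift, the share mediated and the residual correlation are all assumed. The 90% power for the total effect assumes 220 participants with complete data. Exploring mediators by SEM is legitimate. The change should be made, but it does not undermine the design or the sample size.

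**What to change.** 1. State that effectiveness is judged by the intention-to-treat between-arm total effect on follow-up SHE, adjusted for baseline SHE and gender (the stratification factor), and say how this estimate is set against the 5 % threshold.
2. Keep the SEM as a secondary mediation analysis. Adjust it for baseline mediators and baseline SHE, and add a sensitivity analysis showing how the indirect effect changes over a range of residual mediator-outcome correlation.
3. Replace the Discussion sentence with one saying that randomisation identifies the effect of arm on the mediators and on SHE, but not the mediator-to-SHE paths, which rest on assumptions about confounding and temporal order.

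The cost is one regression, one sensitivity analysis and some rewording, with a more modest claim about mechanism. No new data are needed and N does not change: 220 gives about 90% power at d = 0.44 before dropout, even without baseline adjustment.
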